#### 2.2.1. Study Variables 

The main variables of the study can be divided into two main dimensions: (1) cognitive regulation or executive functions: inhibitory control, flexibility, planning, reasoning, and problem solving; (2) emotional regulation: emotional perception and emotional regulation. These variables were, and will be, evaluated through several questionnaires provided to parents, teachers and students and tests performed by children, as shown in Table 1.

Additionally, other sociodemographic data and information about the child’s development and learning history will be collected. Through the “SR-MRehab: Un colegio emocionante”, in each session, the following information will be collected for each task: number of hits, cognitive errors, and the time required by each participant to complete the task.

#### 2.2.2. Pre-Assessment, Post-Assessment and Follow-Up at 6 Months

The instruments that will be used to perform the assessment are described below.

EQ-i: YV [42] is a questionnaire designed to evaluate socio-emotional intelligence in children from 6 years of age. It contains 5 dimensions: intrapersonal intelligence, interpersonal intelligence, stress management, adaptability and general mode. It has been validated with a Spanish population and has shown acceptable psychometric properties, with a Cronbach’s alpha between 0.63 and 0.80 for the different dimensions of the questionnaire.

The NEPSY- II Battery has good psychometric properties and has been adapted and validated with a Spanish population [43]. It allows one to determine neurocognitive development in children and adolescents between 3 and 16 years of age. This tool consists of four subtests: Clock, Design Fluency, Affect Recognition, and Theory Mind. In the Clock subtest, the child is asked to draw a clock, with or without cues. Low scores on this subtest indicate deficits in planning and organization skills, poor visual space ability to draw or read, and poor time perception. The Design Fluency subtest is a non-verbal fluency task in which the child must draw as many unique designs as possible in a time limit, from an initial structure or without structure. Poor performance in this task is related to difficulties in initiating actions and poor cognitive flexibility. In the Affect Recognition subtest, the child is asked to recognize different emotions in different photographs, both freely and in association with other faces. Lastly, in the Theory Mind subtest, the child is shown different photos and asked what he/she thinks the people in the photo are experiencing.

EPYFEI and EPYFEI-Escolar are two questionnaires for parents and teachers, respectively, for the evaluation of children between 3 and 11 years of age. Both have been developed and validated with a Spanish population, with good psychometric properties. These questionnaires can discriminate between different neurodevelopmental disorders in children and allow determining which factors of executive functioning and sensory processing may be most affected. They can both be downloaded from the website enabled by the University of Granada (https://digibug.ugr.es/handle/10481/57781).

The Trail Making Test (TMT) is a neuropsychological test aimed at evaluating attention, psychomotor speed and cognitive flexibility. The Stroke test consists of two parts: part A, in which the child is asked to link 25 numbers in ascending order, arranged disorderly on a sheet. In part B, the child is asked to list the numbers and letters on the page in ascending order and according to the alphabet, that is, number-letter-number-letter. It also has good psychometric properties and different formats adjusted to the age of the child [44].

The Stroop test is widely used in the neuropsychological examination of attention, especially to determine the difficulties in interference inhibition. It has been validated with a Spanish population and is usually employed from the age of 6, or when children have developed good reading skills. For younger children, other formats are available. This test also has good psychometric properties [44].

The assessment will be conducted in the first weeks of December 2020, divided into three blocks. Firstly, the EQ-i:YV questionnaire [42] and the Clock and Affect Recognition subtests of NEPSY-II [43] will be administered to the participants; separately, the teachers and parents will be asked to complete the EPYFEI-Escolar [45] and EPYFEI [46] questionnaires, respectively, which they will have to fill in and give back within the next week. Then, the participants will complete the Design Fluency and Theory of Mind subtests of NEPSY-II. Finally, in a third session, they will carry out a final block to assess executive functions through Trail Making Test A and B (TMT A-B) and Stroop test. 

The same evaluation will be carried out immediately after finishing the program. In addition, the acceptability of the technology will be evaluated with the children at the end of each session and at the end of the whole program. A combination of methods will be used to assess acceptability [47]. Firstly, in each session, each activity will be evaluated using a Smileyometer, which is a visual analog scale with a coding based on a 5-point Likert scale (Horrible = 1; Great = 5). In addition, at the end of the program, the method “*This or That*” will be used, using five questions, for example: ‘What part of the program did you enjoy the most?’, ‘What game would you like to have at home?’ To check the long-term effects of the program, a follow-up will be carried out at 6 months, in which the emotional regulation and executive functioning of the participants will be re-assessed.

#### 2.2.3. Intervention

##### Experimental Group 

The intervention on self-regulation will be carried out through a non-immersive virtual reality platform, “SR-MRehab: Un colegio emocionante”, in which the participants must conduct a series of activities designed specifically for this purpose. These activities will be performed by the children using mainly their hands to manage the virtual objects shown in the screen. To this end, our system makes use of a Kinect motion sensor connected to the computer, to control the body movements of the child. Moreover, our system records some relevant data of the execution of these activities for further analysis of the child’s performance.

The tasks will be divided into two blocks: emotional regulation (ER) and cognitive regulation (CR) (or executive functions), in a total of 10 sessions, once a week, performing a task of each block per session. Each session will last 50 min and will generally take into account the development of the different executive functions (working memory, inhibitory control, flexibility, reasoning, planning and problem solving) [15] and emotional competencies (emotional perception, and emotional self-regulation) [48]. Table 2 and Table 3 show the organization, description and aims of each session for the Experimental and Control Group, respectively. These sessions will take place from January to April 2021.

The principles of the program will be based on the following premises for children with ASD [7,49]: (1) strengthening communicative attempts; (2) choosing the most natural contexts possible; (3) establishing structured and predictable routines and environments; (4) visually supporting information; and (5) adapting our language to the understanding level of the child. Regarding the difficulty of interpreting and responding to social emotions and cues, perspective games are of great interest, where the child and the therapist describe the same object from different perspectives, as well as guessing games (guess what is in this box) and games with social stories, which are short stories that use pictograms to help understand situations with social ambiguity: (1) describing what happens; (2) orienting the action, indicating the child what to do in that situation; (3) anticipating and explaining what can happen and how the child can feel; and (4) developing a strategy that can be applied in similar situations. Virtual stories narrated with puppets can be used in young children. In older children, training techniques may also be used in social skills, with role-playing, theatre, or body expression groups. These activities can be very helpful in teaching skills to predict people’s most likely behavior in certain situations, explaining how people feel, recognizing emotions of joy, sadness, fear, anger, etc., predicting those emotions based on the situation, understanding that emotions depend on desires and beliefs, and assuming someone else’s perspective, which may not match one’s own perspective.

Regarding the executive functions, the proposed activities are intended for the children to notice and detect small changes in the virtual setting, learn a search strategy or visual scan, formulate an action plan, inhibit automatic responses, inhibit distractors to the task (such as noises or irrelevant stimuli for the execution of the activity), increase the maintenance of attention, monitor the activity and the steps taken, predict the consequences of actions, consider alternatives, etc. An example of the tasks is shown in Figure 2.

The MRehab tool allows one to establish five levels of difficulty. Before starting the intervention program, a database will be created with each participant, assigning each of the tasks designed for each child according to the results of the previous assessment.

The intervention will begin with the explanation of the group session of 3 to 4 children. Subsequently, to record the responses and perform the activities, the participants will be asked to perform different tasks, with the support and supervision of the occupational therapist and psychologist. The session will end with a small assembly in which each child discusses his/her experience and how and where the skills learned could be generalized in their activities of daily living. Each session will last one hour.

##### Control Group

The children from the control group will follow a program of emotional education for primary schools, through group activities in the classroom [5,50]. Each session will last 50 min, as in the experimental group. The content of the sessions will include 5 sessions of emotional awareness and 5 sessions of emotional and cognitive regulation. The activities will be similar to those listed in Table 2 for the experimental group, although the virtual reality system will not be used (see Table 3). These sessions will be conducted in parallel in a different room of the school, on the same day and time, carried out by occupational therapists and students from the last year of the degree in occupational therapy.

#### 2.2.4. Outcome Measures

##### Primary Outcome Measure: Emotional Regulation

(1)Emotional Perception

According to the previously presented aims and hypotheses, after performing the intervention protocol, the participants in the experimental group are expected to change in the number of errors in the recognition of recognized emotions on faces in the Affect Recognition subtest of the Children’s Neuropsychology Assessment Battery (NEPSY-II), in which the minimum scores are “0” and the maximum number of errors for children older than 6 years is 79. The higher the score, the worse the recognition of emotions.

(2)Emotional Regulation

The participants in the experimental group are expected to change in their ability to understand mental functions, such as belief, intention, and deficit to understand the relationship between emotions and the social context, according to the Theory of Mind subtest of the Children’s Neuropsychology Assessment Battery (NEPSY-II), in which the minimum score is “0” and the maximum score is 28. The higher the score, the better the ability to mentalize and recognize the mental states of other people.

##### Secondary Outcome Measure: Cognitive Regulation

(1)Cognitive Flexibility

After performing the intervention protocol, the participants in the experimental group are expected to change their shills of maintaining attention and for the ability to change and maintain a new pattern of responses, according to the Auditory Attention and Cognitive Flexibility Subtest of the Children’s Neuropsychology Assessment Battery (NEPSY-II), in which the minimum score is “0” and the maximum score is 30. The higher the score, the number of correct answers, the better the ability to pay attention and to show a flexible behavior with changes. In addition, these subtests allow us to know the number of errors, divided in three types: commission, omission and inhibition errors. The greater the number of errors, the worse the attention and cognitive flexibility. The minimum error score is “0” and the maximum number of commission errors is 189; the maximum number of omission errors is 39 and the maximum number of inhibition errors is 33.

(2)Planning and Sequencing

The participants in the experimental group are expected to change in planning and organization skills, as well as in self-supervision skills, according to the Clocks subtest from Children’s Neuropsychology Assessment Battery (NEPSY-II), in which the minimum score is “0” and the maximum score is 78. A higher score means better skills to plan, sequence and monitor the action.

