**Figure 2 ijerph-17-04198-f002:**
[figure not shown]
Example of tasks with “SR-MRehab: Un colegio emocionante”: (**a**–**c**) Emotional Perception, (**d**,**e**) Emotional Regulation; (**f**) Cognitive Regulation: inhibitory control; and (**g**,**h**) Cognitive Regulation: Reasoning and problem solving.

**Table 1 ijerph-17-04198-t001:** Variables and outcome measures.

Variables	Dimension/Processes	Instruments		Participants		Baseline	During Intervention	Immediately Post-Intervention	24 Weeks Post-Intervention
			Parents	Teachers	Students				
Gender Age Special Needs Diagnosis			X X X	X		X X X X			
Parent’s Educational level			X						
Previous experience with VR and serious games			X		X				
Emotional Regulation	Emotional Awareness	NEPSY-II: Affect Recognition			X	X		X	X
	Emotional Awareness	NEPSY-II: Theory of Mind			X	X		X	X
	Self-regulation	EPYFEI	X			X		X	X
	Self-regulation	EPYFEI-Escolar		X		X		X	X
	Emotional Competencies	EQ-i: YV *			X	X		X	X
Cognitive Regulation/Executive Functions	WM, IC. Pln, Sq	EPYFEI	X			X		X	X
	WK, IC, Pln, Sq	EPYFEI-Escolar		X		X		X	X
	Pl. Sq, Fl	NEPSY-II: Design Fluency			X	X		X	X
	Pl, Sq	NEPSY-II: Clock *			X	X		X	X
	Executive Attention	Trail Making Test A & Trail Making Test B			X	X		X	X
	IC	Stroop Test			X	X		X	X
	Virtual Tasks SR-MRehab	Percent Completed Nº of Errors Type of errors Activity Time Time without interaction Reason for non-attendance or early withdrawal					X X X X X X X		
		Acceptability			X			X	

* Only for children between 7 to 12 years of age. WM: working memory, IC; inhibitory control; Pln: Planning; Sq: Sequencing; Fl: Flexibility.

**Table 2 ijerph-17-04198-t002:** Organization, description and aims of each session for Experimental Group.

Variables/Aims Session	Emotional Regulation	Aim	Description	Cognitive Regulation/Executive Functions	Aim	Description

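### The cognitive-flexibility secondary outcome is defined on a NEPSY-II subtest that the assessment schedule and Table 1 do not include

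*Protocol article*

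**What the plan says.** Section 2.2.4 of the protocol article, under the secondary outcome heading, names two measures of cognitive regulation.

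- **Cognitive flexibility** is assessed "according to the Auditory Attention and Cognitive Flexibility Subtest" of the NEPSY-II. The section gives a score of 0 to 30 correct answers and three error counts with maxima of 189 (commission), 39 (omission) and 33 (inhibition).
- **Planning and sequencing** is assessed on the NEPSY-II Clocks subtest, scored 0 to 78, with no age limit stated.

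Section 2.2.2 describes what is administered. On the NEPSY-II it says: "This tool consists of four subtests: Clock, Design Fluency, Affect Recognition, and Theory Mind". It then sets out three blocks for the children. In the first, alongside the EQ-i:YV, "the Clock and Affect Recognition subtests of NEPSY-II [43] will be administered to the participants". In the second, "the participants will complete the Design Fluency and Theory of Mind subtests of NEPSY-II". The third is to "assess executive functions through Trail Making Test A and B (TMT A-B) and Stroop test". For the post-intervention visit: "The same evaluation will be carried out immediately after finishing the program".

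Table 1 lists each instrument with its time points. Its NEPSY-II rows are Affect Recognition, Theory of Mind, Design Fluency and Clock. The Clock row carries an asterisk, explained as "Only for children between 7 to 12 years of age". The abstract gives the trial's age range as 6 to 11 years.

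**The concern.** An outcome definition and a test-by-test schedule that do not share an instrument cannot both be carried out. If the assessors work from section 2.2.2 and Table 1, the cognitive-flexibility outcome will be empty, and a baseline that was not taken cannot be recovered once the sessions have begun.

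The analyst would then face a named secondary outcome without data and several other executive measures with data: Design Fluency, Trail Making Test A and B, Stroop, and the parent and teacher questionnaires. Choosing among them after the results are known is selective outcome reporting, whatever the intention. In a trial this small, the choice could decide what is reported about flexibility.

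The Clocks question is lesser. It concerns which children the outcome covers, and the document gives two answers.

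**Working it through.** No figure in the plan needs to be reproduced. The check sets the passages side by side.

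**Cognitive flexibility**

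| Place in the protocol article | NEPSY-II subtests named | Auditory Attention and Cognitive Flexibility? |
|---|---|---|
| 2.2.4, secondary outcomes | Auditory Attention and Cognitive Flexibility; Clocks | Yes |
| 2.2.2, description of the battery | Clock, Design Fluency, Affect Recognition, Theory of Mind | No |
| 2.2.2, block 1 | Clock, Affect Recognition | No |
| 2.2.2, block 2 | Design Fluency, Theory of Mind | No |
| 2.2.2, block 3 | None (Trail Making Test, Stroop) | No |
| 2.2.2, post-intervention | Same as baseline | No |
| Table 1, all three time points | Affect Recognition, Theory of Mind, Design Fluency, Clock | No |

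1. The list in section 2.2.2 is closed: it gives the number of subtests and names each one. Blocks 1 and 2 use exactly those four.
2. The post-intervention visit repeats that set, so the subtest is not added later.
3. For the 24-week follow-up, section 2.2.2 says only that emotional regulation and executive functioning are re-assessed. Table 1 gives the instruments for that visit, and the subtest is not among them.
4. As scheduled, the outcome therefore has data at 0 of 3 assessments. This does not depend on the number of children.

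**Scheduled measures that the document links to flexibility.** Section 2.2.2 relates poor Design Fluency performance to poor cognitive flexibility, and Table 1 codes that subtest for flexibility. Section 2.2.2 also says that the Trail Making Test evaluates cognitive flexibility, although Table 1 labels it executive attention. Both are scheduled at all three time points.

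**Clocks**

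1. Clocks is in the battery, in block 1, and in Table 1 at baseline, post-intervention and 24 weeks: 3 of 3 assessments.
2. The abstract's range of 6 to 11 covers six years of age. The Table 1 footnote leaves 7 to 11, which is five of the six.
3. The document gives no age mix, so the number affected is unknown. Taking the planned 26 children as a total and assuming a share *f* of 6-year-olds, the number eligible for Clocks before dropout is 26 × (1 − *f*):
   - *f* = 1/12: 26 × 11/12 = 23.8
   - *f* = 1/6 (ages evenly spread): 26 × 5/6 = 21.7
   - *f* = 1/3: 26 × 2/3 = 17.3

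   These values only illustrate the range; none comes from the document.
4. Block 1 in section 2.2.2 and the definition in section 2.2.4 state no age limit, so they conflict with the footnote.

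**The case against.** The strongest reply is that the document does not say which side is in error. Section 2.2.4 gives full scoring for the subtest, which is what one would expect if the sponsor intends to use it and left it out of the schedule by oversight. That is a fair point. It means that the finding is a contradiction to be resolved, not proof that the outcome will be lost. It does not remove the contradiction, because section 2.2.2 and Table 1 are each written as complete and agree with each other. Nor is this detail that an article leaves to a fuller document: both sides are stated here.

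Three stronger readings are tempting, and the document does not support them.

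- **Neither secondary outcome can be measured.** A reader might infer this from the Table 1 footnote. Clocks is scheduled at every visit, has a stated range and direction, and can be scored in children aged 7 to 11. At most the 6-year-olds are lost.
- **Design Fluency and the Trail Making Test are collected but are not outcomes.** Section 2.2.4 does not name them as secondary outcomes. Table 1, however, presents its contents as variables and outcome measures and lists both under cognitive regulation.
- **Half of the main objective would go unassessed.** Section 1.1.1 does pair cognitive with emotional regulation. But section 2.2.1 and Table 1 spread cognitive regulation over several scheduled tests and questionnaires, and both primary outcome measures, Affect Recognition and Theory of Mind, are scheduled at all three visits.

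**Conclusion.** The point holds for one of the two named secondary outcomes. Cognitive flexibility is defined in section 2.2.4 on a subtest absent from the battery description, the three assessment blocks, the repeated post-intervention assessment and Table 1. If the schedule is followed as written, there are no data for it at any visit, and any substitute would be chosen post hoc. This rests only on comparing the passages; the one condition is that the assessors follow section 2.2.2 and Table 1.

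The Clocks footnote is a minor inconsistency of coverage. If it stands, the outcome applies only to children aged 7 or over. How many children that excludes cannot be said from the document.

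**What to change.** Before the first baseline assessment, make sections 2.2.2 and 2.2.4 and Table 1 name the same instrument for cognitive flexibility. There are two ways.

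1. **Keep the outcome.** Add the Auditory Attention and Cognitive Flexibility subtest to the battery description, to one of the assessment blocks and to Table 1 at all three time points. The cost is a little more testing time per child at each visit.
2. **Redefine the outcome.** In section 2.2.4, replace it with one flexibility measure that is already scheduled, Design Fluency or Trail Making Test B, and state its score range and direction. This adds no testing. The cost is a somewhat different construct: the present definition concerns sustained attention and shifting to a new response pattern, while Design Fluency is described as a non-verbal fluency task. A registry update may be needed.

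If the sponsor intended the named subtest, the first option keeps the outcome as defined. In either case, a single measure should be fixed before any data are seen.

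For Clocks, reconcile the Table 1 footnote with the 6 to 11 age range and with the unrestricted wording of sections 2.2.2 and 2.2.4. If the footnote stands, state in section 2.2.4 that the outcome applies to children aged 7 or over at baseline. The EQ-i:YV carries the same asterisk although section 2.2.2 describes it as suitable from age 6, so it should be checked at the same time. This costs only wording.

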### 2.3. Data Mangement

The data will be collected from the results obtained in the assessment tests and questionnaires that will be provided to the parents and teachers, being subsequently introduced in SPSS, assigning each student a confidential code based on their school year and always respecting their anonymity. The data manager will create the database in SPSS, debug the database and perform all data analyses. The data manager will be blinded to the randomization of the participants.

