#### 2.4.2. Data Analysis Plan

A descriptive analysis will be carried out for all the variables in the study. The qualitative variables will be described with absolute frequencies and percentages for each of their categories, and quantitative variables with mean, standard deviation (DE), maximum and minimum values, as well as median and interquartile range, where appropriate. The corresponding 95% confidence intervals (ICs) will be calculated. The normality of the continuous variables will be verified using graphical methods and normality tests.

The Chi-square test will be used to study the statistical significance of the differences between proportions. To study the statistical significance of the differences between means, different tests, questionnaire scores, completion time and number of errors of each virtual task throughout the different sessions, the following tests will be used depending on whether or not the variables to be compared show normality: Student’s t test, Mann–Whitney U-test, ANOVA or Kruskal–Wallis test. Furthermore, the effect size of the changes observed will also be calculated. The analysis of the association between two quantitative variables will be performed, using Pearson’s or Spearman’s correlation coefficient, depending on whether or not the variables show normality.

If necessary, generalized linear regression models will be used to adjust the results for any confounding covariate that shows significant baseline differences between the groups and a correlation with the result. For the hypothesis testing, a significance level of 5% will be assumed (*p* < 0.05). All statistical analyses will be carried out using the IBM SPSS software (version 24, IBM Corporation, New York, NY, USA).

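### The data manager is declared blinded without qualification, but is also given the analysis of task data that only the virtual reality arm can produce

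*Protocol article*

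**What the plan says.** Section 2.3 (Data Management) describes one role: "The data manager will create the database in SPSS, debug the database and perform all data analyses". It then says of that role: "The data manager will be blinded to the randomization of the participants". No stage of the work and no part of the data is excepted.

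The same section describes what is entered into SPSS: "The data will be collected from the results obtained in the assessment tests and questionnaires that will be provided to the parents and teachers". Session logs are not named there. Each child receives one confidential code.

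Section 2.2.1 says that, through the SR-MRehab system, "in each session, the following information will be collected for each task: number of hits, cognitive errors, and the time required by each participant". Table 1 lists the corresponding items under "Virtual Tasks SR-MRehab". The Control Group section says that activities are similar to those of the experimental arm, "although the virtual reality system will not be used".

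Section 2.4.2 includes time and error counts on the virtual tasks, across sessions, among the quantities to be tested. It chooses between parametric and rank tests from graphs and normality tests. On covariates it says: "If necessary, generalized linear regression models will be used to adjust the results" for confounders that meet a stated criterion.

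On acceptability, section 2.2.2 says that "the acceptability of the technology will be evaluated with the children at the end of each session" and again at the end of the programme. That sentence names no arm.

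**The concern.** Blinding the analyst is meant to keep knowledge of allocation out of decisions made while handling the data: which values are queried or corrected, how a borderline normality plot is read, whether an adjusted model is called for. Here the person making those decisions is also assigned data whose mere presence identifies the arm.

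This is the only blinding claimed in the text shown, so a reader will give the trial credit for it. Section 2.4.1 gives a final sample of 26 children. Read as the total, that is about 26 / 2 = 13 per arm, although simple randomization does not guarantee equal arms. In an arm of 13 each child carries 1 / 13, or about 8%, of the group mean, so a decision about a single record is not negligible.

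**Working it through.** There is no figure of the plan to reproduce. The check is whether the statements can all be true together.

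1. **Who does what.** Section 2.3: one data manager builds the database, cleans it and does every analysis, and is blind to allocation.
2. **What the analyses include.** Section 2.4.2: virtual-task times and errors are among them. With step 1, the data manager analyses those data.
3. **Who can have such data.** Section 2.2.1 and Table 1: they are recorded by the SR-MRehab system. Control Group section: controls do not use it. A child with any virtual-task record is therefore in the VR arm.
4. **What absence means.** A child with no record is a control, or a VR child who attended no session. The pattern of recorded and missing task data thus shows allocation for essentially every child who attended.
5. **Does a separate file alone prevent this?** No. If the logs carry the same child code as the outcome data, the list of codes in the log file is the list of VR children. A different code is needed, or the logs must be withheld until later.
6. **Does the article set such an arrangement?** It describes no second code, no second analyst and no order in which the data manager receives the files.

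Steps 1 to 4 show that the unqualified statement cannot be true for the whole of the assigned work. Steps 5 and 6 show that whether it is true for the between-arm comparison depends on an order of work that the article does not give.

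The decisions exposed if the VR data come first are the cleaning of the outcome data, the reading of normality from graphs and tests together, and the judgement that adjustment is needed.

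**The case against.** The strongest reply is that the outcome comparison may well be blinded in practice. Section 2.3 names only tests and questionnaires as SPSS inputs, and the VR platform keeps its own records. The primary and secondary outcomes are test scores collected in the same way in both arms, so they could be cleaned and compared under an A/B code before anyone opens the logs. File handling is also the kind of detail that a condensed article leaves to a fuller document. This stands as far as it goes: nothing shows that the logs are merged into the outcome file. It does not rescue the statement as written, which covers one person, all analyses and no time limit.

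A reader might also infer more than the text supports:

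- *That allocation is known for all 26 children when the arms are compared.* This would require the logs to be linked to the outcome data beforehand, which the article does not say. A VR child who never attended would also not be identified.
- *That acceptability ratings exist only in the VR arm.* The wording about technology and the place of the item in Table 1 make this likely, but no sentence restricts it, and ratings of activities could be asked of controls. The point does not need it.
- *That the analysis is left wide open.* The covariate sentence gives a two-part rule: a significant baseline difference and a correlation with the outcome. The flexible wording on medians and interquartile ranges concerns descriptive summaries only. Test choice is tied to normality, which can be judged without knowing the arm. The remaining discretion is real but narrow.
- *That outcome scoring is unblinded.* The statement concerns the data manager, and the conflict shown here has no bearing on who scores the tests.

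**Conclusion.** The point holds in a limited form. The article states a safeguard without qualification and assigns the same person work that is incompatible with it. The blinding cannot hold for the virtual-task analyses. For cleaning, test choice and adjustment it holds only if those steps are complete before the VR data are seen.

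This rests on two readings: that the assignment of all analyses in section 2.3 includes the virtual-task analyses of section 2.4.2, and that controls generate no SR-MRehab records, which follows from their not using the system. Once the logs are opened under a linkable code, allocation is revealed for essentially every attending child. The effect on the trial's results cannot be computed from the document, and no bias is shown to have occurred. The matter should be corrected because the claim is one that readers rely on and the correction is easy. It does not invalidate the design.

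**What to change.** State in section 2.3 that:

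- the SR-MRehab logs, and any acceptability ratings collected only in the VR arm, are kept by the intervention team in a separate file under a different code, with the linking key held away from the data manager;
- the data manager receives the test and questionnaire data with arms labelled A and B;
- the VR file, the key and the arm labels are released only after the outcome data are cleaned and locked and the between-arm comparison, including the choice of test and any adjustment, has been run.

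Analyses of task performance, and any correlation of it with outcomes, follow that release.

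If this is not wanted, limit the blinding statement to the outcome dataset up to the between-arm comparison and keep to that order of work, or remove the statement.

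The cost is one extra file and one release step. No additional staff or children are needed. The descriptive VR results become available somewhat later.
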